### Self-report measures and covariates

Though the focus of this study is *objective* measurement, standard surveys items were administered for comparison with prior studies, because some perceptions e.g. safety and aesthetics are not available in objective GIS layers, and to assess important covariates. Surveys were provided in Spanish and English depending on language preference of the participant.

Demographic covariates include age, income, gender, ethnicity, education, employment status, employment location, marital status, number of children in the household, automobile ownership, driving status, type of residence, and years living at address. Family history of cancer was assessed with a standard population based surveillance survey [62], and employed as a covariate in analysis. Subjects were asked to record the names of all medications (prescription and over-the-counter) they currently take, and the doses of each (amount per day etc.). Participants were asked if a health professional ever diagnosed them with a chronic disease or risk factors. The Center for Epidemiologic Studies Depression Scale was included to assess symptoms of depression [63]. International Physical Activity Questionnaire *(*IPAQ *-* long form) assessed participants’ reported PA over the last 7 days. The IPAQ estimates PA frequency and duration per week for housework, occupation, transportation, and recreation [64]. The IPAQ includes a measure of total duration of weekday and weekend sitting time. Frequency and duration of sedentary behaviors were also be assessed by a separate 7-item measure [65]. Sleep disturbances was assessed using the NIH PROMIS Sleep Disturbance 6a Short Form and the MAP Index/ Survey Screen for Sleep Apnea. Quality of sleep was assessed using the Epworth Sleepiness Scale.

Due to the importance of the neighborhood design, an 11-item self-selection survey was deployed that measures reasons for moving to a neighborhood, which is a commonly cited potential bias in cross-sectional environmental studies [66]. Social interactions was measured using items from standard surveys assessing social isolation, cohesion, and support [67, 68]. Late Life Functioning Disability Instrument (LLFDI) was used to determine self-reported functional performance and physical disability [69]. The validated and widely used NEWS [70] was used to assess perceptions of neighborhood environment variables including subscales for aesthetics, and perceived safety from traffic and crime. The NEWS has good test-retest reliability (median ICC = .79) and construct validity by discriminating known neighborhood types and showing convergent relations to PA. Participants completed the NEWS scale for both home and work locations. For those who work, surveys were given related to support in the workplace for healthy food, physical activity and standing. The home sleep environment was assessed by the Functional Outcomes of Sleep Questionnaire (FOS-Q). Home sedentary environment included number of TVs in the bedroom etc.

### Sample size

Sample-size estimates were computed to achieve ≥80% power to detect meaningful differences in associations between outcomes and dynamic versus static GIS exposures. Specifically, a sample-size of 648 would achieve 80% power to detect a 0.32 correlation between outcome, Y, and Dynamic GIS-based neighborhood attributes (X) versus a 0.15 correlation between the outcome Y and Static GIS exposure (W). These calculations, based on the methods of Dunn and Clark [71] for dependent correlations, assumed a conservative correlation of 0.2 between the static and dynamic GIS-measures, and used a stringent significance level (α = 0.01 2-sided) to account for the multiple outcomes (BMI, MVPA, walking, and biomarkers). Further, accounting for census-block clustering effects with ICC = 0.05 to 0.1, we would require 630–660 participants. Recruitment was targeted at 700 individuals. Due to the intense data collection requirements, limited recruitment options due to environmental limitations (walkability and fast food access), and difficulty in recruiting Hispanic participants, recruitment fell short of the targeted 700 and the study was completed with 602 participants.

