## Methodology

### Study design

This is a cross-sectional observational study conducted in San Diego County, California. Participants were randomly sampled from urban census block groups purposefully selected to maximize environmental variability in walkability and fast food access (as a proxy for healthy eating environments), and to strengthen our ability to uncover associations with cancer related outcomes. Walkability was derived from the San Diego Association of Governments’ (SANDAG) 2012 Health Atlas [40], which calculates a walkability index from net residential density, intersection density, retail floor area ratio, and land use mix. Versions of this index have been validated [41]. Data on food retail was obtained from San Diego County’s Department of Environmental Health’s Food Facility Inspection database in 2013. Terciles for walkability and fast food were calculated, and four categories were created using the highest and lowest terciles resulting in 764 census block groups for participant recruitment out of 1794 total in San Diego County: high fast food/low walkability (38 block groups), high fast food/high walkability (318), low fast food/low walkability (319), and low fast food/high walkability (89). No more than 10 participants per census block group were recruited. Recruitment began in 2014 and ended in 2017.

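### The sample-size figures are inconsistent: the clustered requirement (630–660) starts below the pre-clustering 648, and the stated inputs give about 594; power at the completed 602 is not restated

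*Protocol article*

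**What the plan says.** All the figures are in the protocol article, mostly under Sample size.

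- The aim is given in planning terms: "Sample-size estimates were computed to achieve ≥80% power to detect meaningful differences in associations".
- The first number is "a sample-size of 648 would achieve 80% power to detect a 0.32 correlation between outcome, Y" and the dynamic exposure, set against 0.15 for the static exposure. The method is Dunn and Clark's for dependent correlations at two-sided alpha 0.01, and the calculation "assumed a conservative correlation of 0.2 between the static and dynamic GIS-measures".
- The clustering statement comes next: "Further, accounting for census-block clustering effects with ICC = 0.05 to 0.1, we would require 630–660 participants". No mean cluster size is given. The only information on cluster size is under Study design: "No more than 10 participants per census block group were recruited".
- The target was 700. The outcome is disclosed: "recruitment fell short of the targeted 700 and the study was completed with 602 participants". The Discussion repeats the shortfall against 700. Neither place gives power at 602.

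Statistical approach names the dynamic-versus-static comparison as the main objective, to be tested by the same Dunn and Clark method, with GEE models that adjust for block-group clustering.

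**The concern.** The clustering sentence is worded as a further step after 648, yet its lower end is 18 below 648 and its upper end only 12 above. With a positive ICC and more than one person in some block groups, a clustering allowance can only raise the requirement. At least one of the figures is therefore wrong or wrongly described, and the reader cannot tell which.

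This is the only power statement for the study's main objective. If the dynamic-versus-static comparison shows no clear difference, readers will judge that result against this paragraph. They need to know what requirement 602 should be compared with, and what difference 602 participants could detect.

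**Working it through.** **Inputs.** From Sample size: r1 = 0.32 (outcome with dynamic), r2 = 0.15 (outcome with static), rx = 0.2 (static with dynamic), two-sided alpha 0.01, power 80%, ICC 0.05 to 0.1. Not stated: mean participants per block group (m).

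**Step 1. Try to reproduce 648.** For two Fisher-z correlations that share a variable:

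N = 3 + 2(1 − c)(z₁₋α/₂ + z_power)² / (atanh r1 − atanh r2)²

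where c = ψ / [(1 − r1²)(1 − r2²)] and ψ = rx(1 − r1² − r2²) − ½ r1 r2 (1 − r1² − r2² − rx²).

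- atanh 0.32 − atanh 0.15 = 0.3316 − 0.1511 = 0.1805
- ψ = 0.1550, c = 0.1766, 2(1 − c) = 1.6467
- (2.576 + 0.842)² = 11.679
- N = 3 + 1.6467 × 11.679 / 0.03258 = 593.3, so 594

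Variants at the same alpha and power (pooled covariance, untransformed correlations, Williams' t) give 587 to 596. None gives 648.

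**Step 2. Power without clustering.** Power = Φ(0.1805 × √[(n − 3)/1.6467] − 2.576).

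| n | Formula | Simulation (20,000 replicates) |
|---|---|---|
| 602 | 80.7% | 81.0% |
| 648 | 84.1% | 84.2% |

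**Step 3. What does 630–660 imply?** Use the design effect 1 + (m − 1) × ICC.

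- From 648: 630/648 = 0.972, a deflation, which is impossible. 660/648 = 1.019, which at ICC 0.1 means m ≈ 1.2. With m = 2, a base of 648 would need 680 to 713.
- From 593.3: 630/593.3 = 1.062, so m ≈ 2.2 at ICC 0.05. 660/593.3 = 1.113, so m ≈ 2.1 at ICC 0.1. The two ends agree.
- Solving both ends for one base and one m gives base = 2 × 630 − 660 = 600 and m = 2 (600 × 1.05 = 630; 600 × 1.10 = 660).

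So the clustered range is coherent with a base of about 594 to 600 and about two people per block group. It does not cohere with a base of 648.

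**Step 4. Power at 602 on the plan's own clustered range.**

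| Clustered requirement | Design effect (base 593.3) | Effective n at 602 | Power | Dynamic correlation detectable against 0.15 with 80% power |
|---|---|---|---|---|
| none | 1.000 | 602 | 80.7% | 0.319 |
| 630 | 1.062 | 567 | 77.8% | 0.324 |
| 660 | 1.113 | 541 | 75.4% | 0.328 |

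Power at 602 drops below 80% once the design effect passes 602/593.3 = 1.015, that is m above about 1.3 at ICC 0.05 or about 1.15 at ICC 0.1.

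**Step 5. Sensitivity to rx.** At design effects of 1.05 to 1.10, power at 602 is 70–72% if rx = 0.1, 76–78% if rx = 0.2, and 82–84% if rx = 0.3.

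**The case against.** **The document does not claim that 80% was achieved.** This stands. The 80% wording describes how the size was planned, and the shortfall and its reasons are disclosed. A reader can see that 602 is below 630. What is missing is power at 602.

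**Missing 648 proves nothing about power.** This also stands. A reader might infer that because 602 is below 630, 648, 660 and 700, the planned power was lost on every count. But 648 is larger than the stated inputs require, and on those inputs 602 is enough without clustering. Only the clustered range supports a shortfall.

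**Much lower power is not shown.** A reader might take the limit of 10 per block group, or the 38 block groups in the smallest stratum, and compute power between 47% and 74%. Those figures are hypothetical. Ten is a cap, and filling every cluster to it would mean about 60 of the 764 eligible block groups. Four per block group assumes that a quarter of the sample came from the 38, which the article does not say, and applies that stratum's cluster size to everyone. If the sample were split in quarters and spread evenly over the 38, 89, 318 and 319 block groups, the mean cluster sizes would be 3.96, 1.69, 1 and 1. The person-weighted mean is then (3.96 + 1.69 + 1 + 1)/4 = 1.9, close to the two implied by 630–660.

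**648 may be explicable.** It lies inside 630–660 and may already include clustering. Rounding of the printed inputs could also matter: 0.315 with 0.155 would require 670. Neither explanation rescues the paragraph as written. If 648 includes clustering, the clustering sentence is not a further step and no base is given. If 648 is a true base, 630 is still too low.

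**The design effect may be overstated.** Dynamic exposure comes from each person's own GPS trace, so it is not fully shared within a block group, and the simple formula is then an upper bound. This is fair, and is a reason to report a range.

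**Conclusion.** The inconsistency is real and visible in the text: a clustered range beginning at 630 cannot follow from an unclustered 648. The stated inputs give about 594, so 648 is about 9% too high (648/594 = 1.09) if it is meant as the unclustered requirement for 80% power. The documents do not settle whether 648 is an error, a figure that already includes clustering, or the product of inputs printed differently from those used.

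At 602, power is about 81% without clustering and about 75–78% against the plan's own clustered requirement, a loss of 2 to 5 points from the planned 80%. The detectable dynamic correlation moves only from 0.319 to 0.324–0.328, against a planned 0.32.

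These figures assume that the printed correlations and alpha are right, that the simple design effect applies, that about two people per block group underlies 630–660, and that all 602 have analysable exposure and outcome data. The exposure correlation could move power in either direction. The documents do not support a conclusion that the study is badly underpowered.

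**What to change.** 1. Reconcile 648 with 630–660. If the printed inputs are right, the unclustered requirement is about 594. If 648 already includes clustering, say so and give the base. If an input was rounded or misprinted, correct it.
2. State the mean number of participants per block group behind 630–660.
3. State power at 602, and the smallest dynamic correlation detectable against 0.15 with 80% power, using the realised cluster sizes and ICC 0.05 to 0.1. Add a line on sensitivity to the correlation between static and dynamic exposure.

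The cost is a short recalculation and a rewritten paragraph. It needs no extra participants, no new data and no change to the planned analyses. The stated power will probably be slightly less favourable.

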### Statistical approach

Our main objective is to compare Dynamic and Static GIS measures of PA and food environments and their associations with PA behaviors, BMI, diet, and biological markers. To test if the Dynamic GIS exposures are more strongly correlated with outcomes than the Static measures, we will apply the methods of Dunn and Clark [71] for dependent correlations (e.g., comparing two correlations which have a common variable, i.e., the PA behaviors or biomarkers). In addition, we will fit generalized estimating equations (GEE) models to examine associations between exposure to PA supportive environments (main effect) and outcomes (PA, BMI, diet, biomarkers) with adjustment for individual level confounding covariates (e.g. demographics, medication use for biomarker analyses), and block group clustering effects. We will use the multiple-informant approach developed by Horton et al. [72] to test if regression coefficients between PA and outcomes differ for the dynamic vs static GIS measures. We will examine interactions between covariates (e.g., ethnicity, age) and GIS measures on outcomes, to test if these factors moderate exposure-outcome associations. Similar analyses will be conducted for the self-reported outcomes, and Static versus Dynamic GIS measures of healthy eating promoting environments.

### Data storage and dissemination

Due to the sensitive nature of the GPS data collected, as well as the significant volume of data generated from the sensor devices, a secure geodatabase is used to store and process the GPS and accelerometer data. The geodatabase is housed in a HIPAA and FISMA-compliant (HIPAA Privacy Rule establishes national standards for protection individual medical records and personal health information) private computing cloud housed at the San Diego Supercomputer Center called Sherlock (http://sherlock.sdsc.edu). The geodatabase employs PostgreSQL to organize spatial data, and allow them to be directly exported to spatial software for visualization purposes [73]. All other data will be stored in a secure database, stripped of identifiers. Methods for data management and coding can be obtained by contacting the corresponding author. The results of the study will be disseminated through publications, reports, and conference presentations.

## Discussion

Understanding PA and dietary behaviors in the context of their environments can provide evidence leading to the design of potentially more effective multi-level interventions that can be designed to mitigate disparities in cancer outcomes. There are, however, still many limitations in the design and implementation of cross-sectional studies that examine PA and dietary behaviors in environmental contexts. There are no studies with extensive objective measures of behavior, environment, and exposure that also assess cancer-related biomarkers. The study is cross-sectional, limiting inferences of causality between outcomes. However, the environmental design and objective measurement of environmental exposures allows for more accurate assessment of associations between environment, behavior, and cancer-related biomarkers.

The Community of Mine study collected minute-level PA, sleep, and location data, food recalls, biomarkers, and survey information for 602 participants through a purposeful neighborhood-based sampling design, as well as extensive environmental information for the study area. The study protocol has completed data collection and is now moving into the data analysis phase of the study. It is important to note that there were significant challenges involved with data collection stemming from the large demands placed on participants (sensor device wear and clinical visits), limitations on location of recruitment (census block group walkability and fast food access selection design), and recruitment of Hispanic individuals. The location component of recruitment was purposeful to attempt to expand the variability in types of environments that participants lived in. However, with study results we hope to demonstrate that this may be an unnecessary recruitment limitation when the addition of GPS data may provide significant environmental exposure variability. While recruitment fell short of the 700 participant goal, the resulting data set is rich in objective measurements of health behaviors and biomarker outcomes. The main goal of the study is to advance methods of cancer risk exposure assessment by comparing the utility of static versus dynamic environmental exposures assessed by integrating GPS and GIS data. The data collected will allow for several other analyses of environmental exposure effects, such as time spent indoors and outdoors, interlinking effects of sleep duration/quality, PA, and diet, as well as environmental and racial inequalities as related to cancer risk.

## Abbreviations

CPM: Count per minute
ESRI: Environmental Sciences Research Institute
FOS-Q: Functional Outcomes of Sleep Questionnaire
GEE: Generalized estimating equations
GPS: Global positioning system
IPAQ: International physical activity questionnaire
KDE: Kernel Density Equation
LLFDI: Late Life Functioning Disability Instrument
NDSR: Nutrition data system research
PA: Physical Activity
PALMS: Personal Activity and Location Measurement System
SANDAG: San Diego Associations of Governments
